##### Registry follow-up

After the last 18-month follow-up, the study dataset will be sent to Statistics Denmark with a list of all invited participants to allow a non-participant analysis and long-term follow-up. The study data will be linked with data from the Danish Civil Registration System [76] e.g., the DNPR [57], the Danish National Prescription Registry [55, 56], and other registries indexing, e.g., hospital admittance, diagnosis- and treatment codes, prescription medications, employment status, living situation (e.g., partner information), and income. We will also examine diagnostic stability [77], e.g., change of primary diagnosis from first episode depression to an anxiety or personality disorder or later recurrent depressive episode or conversion to bipolar affective disorder.

### Statistical analyses

We plan to investigate the outlined hypotheses using both data- and hypothesis-driven approaches. We will publish more specific analysis plans on the web (e.g., PROSPERO) before starting detailed analyses.

#### Data-driven analyses

We will use machine learning algorithms to determine a combination of baseline characteristics that best predict treatment outcomes. In contrast to hypothesis-driven analyses, data-driven machine learning frameworks enable us to identify novel associations between patient characteristics and treatment response and interactive effects of complementary patient characteristic information in prediction. Recent interest in machine learning approaches to prediction is to develop *classifiers* that combine a range of patient-level data to provide a patient-level prediction of treatment response. The most common classifiers are based on patient characteristics or biomarkers assessed before treatment initiation [78, 79]. This information may be used in clinical settings to select a specific treatment if it is predicted to have a higher chance of success or to suggest that a patient may generally be treatment-resistant, which could justify earlier use of second-line therapies [26].

In the present study, we will first use machine learning to train classifiers based on broad non-imaging data collected from all patients in the cohort. Neuroimaging data from EEG, MRI, and PET in subcohorts I and II will subsequently be included, enabling us to make meaningful statements about the marginal improvement in model performance with or without specific neuroimaging measures. This is critical for optimising patient care with costs associated with data acquisition. Following the recommendations for best practice [80, 81], we will employ randomized k-fold nested cross-validation, i.e., splitting the collected data into training and testing datasets that reported model performance measures are not upwardly biased due to data leakage.

We will use latent class analysis to identify different MDD subgroups that share characteristics measured at baseline (hypotheses 1.2 and 2.3) [25, 82, 83]. To investigate if adding neuroimaging data improves clustering (hypothesis 2.3), we will compare the heterogeneity of change on clinical outcome, i.e., mean and variance.

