Previous studies have focused primarily on individual course predictors from just one or two domains, e.g., genetic [13], structural and functional neuroimaging [14–18], electroencephalographic biomarkers [19, 20], blood markers [21], cognitive disturbances [22, 23], and demographic or clinical data [24, 25]. So far, no single marker has proven reliable enough to be implemented in clinical practice [19, 26]. A multimodal approach to depression is essential as the disorder's aetiology is likely multi-causal. That is, prediction models that combine multiple candidate biomarkers might have more predictive utility [24], but must still be generalizable and cross-validated across different cohorts [27]. Other issues include small sample sizes, using data from randomised control trials, lack of clinically and biologically relevant predictive markers, short follow-up time, and poorly validated and biased prediction models [9, 26, 28].

So far, most studies have focused on predictors of response to pharmacological antidepressant treatment without examining the effect of other commonly used treatment modalities such as psychotherapy. Factors such as safety, tolerability, and the effect of the patient's preferences (e.g., dislike of medication or psychotherapy) on overall treatment outcome are also underexplored [26]. Together with substantial methodological variance across studies, these limitations have hampered the ability to draw ecologically relevant and generalizable conclusions from meta-analyses [26, 29, 30].

With this cohort-based study, we will generate a large longitudinal observational multi-modality clinical dataset that allows for a thorough analysis of which phenotypic components enable the best participant stratification for optimal treatment success. We will leverage the Danish healthcare system, which provides standardised treatment packages for all patients. Currently, group cognitive-behavioural therapy (CBT) constitutes the backbone of the treatment package with possibilities for initiation or changes in pharmacotherapy. The treatment package is nationally uniform and designed by Mental Health Services in the Capital Region. The treatment package was introduced in 2013 and revised in 2017 based on clinical and patient experience. However, while the treatment components in the package are research and evidence-based, the treatment effect in real life has not been examined.

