### Objectives

The primary objective of this study is to identify single or composite biomarkers that can reliably identify clinical profiles of MDD and predict their treatment outcomes.

To achieve this aim, we will establish a large, single-site cohort of adult patients diagnosed with first-episode MDD and referred for a treatment package for first-episode depression in secondary care, phenotyping patients before treatment initiation. All patients in the cohort (*n* = 800) will contribute with basic clinical, cognitive, psychometric, and biological data, i.e., genetics and blood biochemistry. A subcohort (subcohort I, *n* = 600) will provide Magnetic Resonance Imaging (MRI) and Electroencephalogram (EEG), and a second subcohort (subcohort II, *n* = 60) of subcohort I with patients unmedicated at inclusion will also undergo a Positron Emission Tomography (PET) brain scan with the presynaptic PET tracer [^11^C]-UCB-J. Clinical depression symptom severity is assessed with the Quick Inventory of Depressive Symptomatology (QIDS) at baseline (T_0_), and 6 (T_1_), 12 (T_2_) and 18 (T_3_) months after treatment initiation (Fig. 1). The treatment package typically lasts six months.

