## Methods and design

### Setting

The Capital Region of Denmark has a population of 1.6 million people. Patients in the Capital Region of Denmark are referred by their general practitioner (GP) or other treatment providers to a central diagnostic and referral centre within the mental health services that yearly assesses 20.000 referrals. About 4000 patients are further evaluated in person and diagnosed by the centre.

Five mental health centres in the region provide treatment packages for first-episode depression and will include participants in the study. The Mental Health Centre Amager and the Copenhagen centre consisting of two clinics located in the City of Copenhagen and treat approximately half of all patients, whereas Ballerup and Glostrup treat approximately a third of patients in the surrounding suburb (Sup. Figure 2). The Psychiatric Centre Northern Zealand treats approximately 16% of patients and is located north of Copenhagen, in a region of intermediate urbanisation with individual municipalities classified as rural.

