### Study population

We aim to establish a cohort of 800 patients referred to the Danish treatment packages for unipolar first-episode, non-psychotic depression during 2021–2025. We recruit patients from all six clinics in the region. Each clinic receives approximately 100–250 treatment referrals yearly, and approximately 1100 patients are referred yearly. Approximately 80% of referrals are sent directly to the clinics. Patients are recruited during evaluation at the central diagnostic and referral centre or the first consultation in the clinics. Approximately 88% of referrals result in treatment package initiation.

During 2019–2020, 37% of patients were on an antidepressant (usually the selective serotonin reuptake inhibitor (SSRI) Sertraline from their GP) when starting the treatment package, and 54% of patients ended the treatment package on an antidepressant medication. 13% of patients were transferred to a treatment package for a different primary diagnosis group, e.g., generalised, social anxiety, post-traumatic stress disorder, emotionally unstable personality, avoidant personality disorder, eating disorder or obsessive–compulsive disorder. 20% dropped out of treatment. 5% of patients were hospitalised during their treatment package; hospitalization does not preclude the continuation of the treatment package.

The treatment package is a program with manualised psychotherapy in groups of eight patients as the core treatment module together with psychoeducation for the patient and relative (Sup. Table 1). In brief, a treatment package consists of 15–18 h: 2–3 h of initial workup followed by 6 h of individual therapy or 12 sessions of 2 h group therapy (8 patients per group); 1–2 h of engagement and psychoeducation of relatives; 1–5 h of medication clinic; and 2 h of relapse prevention. The program is designed around group-based CBT, but clinics also offer alternatives to CBT, e.g., psychodynamic and schema therapy, and groups for specific demographics, e.g., men or adolescents, and individual therapy. Medication is available as needed.

The research and assessment at baseline for recruited participants is conducted at the Neurobiology Research Unit (NRU) at the Copenhagen University Hospital Rigshospitalet and followed by clinicians from the Mental Health Centre Copenhagen who are not involved in the patient's treatment.

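### Random cross-validation folds across six treating clinics cannot separate patient-level prediction from clinic differences or show transport to another clinic; add leave-one-clinic-out results

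*Protocol article*

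**What the plan says.** Under Objectives the article says "we will establish a large, single-site cohort of adult patients". Study population says "We recruit patients from all six clinics in the region", and Setting says "Five mental health centres in the region provide treatment packages for first-episode depression and will include participants in the study". One of the five centres has two clinics, so the counts of five and six agree.

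The catchments differ. The clinics in the City of Copenhagen "treat approximately half of all patients, whereas Ballerup and Glostrup treat approximately a third of patients in the surrounding suburb", and the Northern Zealand centre, with about 16% of patients, serves an intermediately urbanised area that includes rural municipalities. Baseline research assessment takes place at one research unit; treatment is given in the clinics.

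For the classifiers, Data-driven analyses says "we will employ randomized k-fold nested cross-validation, i.e., splitting the collected data into training and testing datasets", and that reported performance will therefore not be inflated by leakage. Neither that section nor any other names clinic as a fold unit, stratum or covariate. The same section aims at predictions for the individual patient that could inform choice of treatment. Background sets the standard that models combining several biomarkers "must still be generalizable and cross-validated across different cohorts".

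**The concern.** With random folds, every clinic appears in both training and test data. If remission differs between clinics, any baseline feature whose distribution differs by catchment can earn predictive credit by standing in for the clinic. The baseline data include such features: ethnicity, education and occupational history (Questionnaires; Medical records and registry data). Nested splitting prevents tuning from contaminating testing. It does not address this issue, because the association is genuine within these six clinics.

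Two statements are at stake: that a marker predicts the patient's own outcome, and that the model would work elsewhere. Hypothesis 2.2 rests on an incremental gain from EEG and MRI, so even a few hundredths of AUC could matter if the added features also track catchment.

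**Working it through.** The article gives no performance target and no clinic-level outcome rates, so there is no stated figure to reproduce. The check has three parts.

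**1. Clinic figures**
- Shares: 1/2 + 1/3 + 0.16 = 0.993, so the areas account for all patients within rounding.
- Referrals: 6 × 100 to 6 × 250 = 600 to 1,500 a year, which covers the stated 1,100.
- Expected patients per clinic out of 800, with an equal split within each area (assumed): city 800 × 0.5 / 3 = 133; suburb 800 × (1/3) / 2 = 133; Northern Zealand 800 × 0.16 = 128.
- If recruitment instead followed the stated referral extremes: 800 × 100/1,100 = 73 to 800 × 250/1,100 = 182.

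Holding out one clinic at a time is feasible.

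**2. Size of the effect (simulation, assumed inputs)**

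Both set-ups use 800 patients, six clinics, a ridge logistic classifier, random 10-fold cross-validation and 150 replicates per setting. Clinic differences enter as a normal deviation in the log-odds of remission. To interpret its SD: six normal draws have an expected range of about 2.53 SD, so with mean remission of 35% (assumed; logit −0.62) the expected lowest and highest clinic rates are expit(−0.62 ± 1.265 × SD).

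*Set-up A: a real patient-level signal (AUC about 0.61) plus features that identify the clinic*

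| SD of clinic log-odds | Implied clinic rates | Random folds | Leave-one-clinic-out | Difference |
|---|---|---|---|---|
| 0 | 35% | 0.601 | 0.606 | −0.005 |
| 0.3 | 27–44% | 0.618 | 0.606 | 0.012 |
| 0.5 | 22–50% | 0.640 | 0.605 | 0.035 |
| 0.7 | 18–57% | 0.671 | 0.606 | 0.065 |

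When features encode the clinic only weakly, the largest difference is 0.611 − 0.598 = 0.013 (SD 0.5); the others are at most 0.005.

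*Set-up B: no patient-level signal; ten features whose means differ by clinic, moderately (SD 0.5) or strongly (SD 1.0)*

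| SD of clinic log-odds | Random folds, moderate | Random folds, strong | Leave-one-clinic-out |
|---|---|---|---|
| 0 | 0.490 | 0.491 | 0.499–0.500 |
| 0.2 | 0.499 | 0.507 | 0.499 |
| 0.4 | 0.519 | 0.543 | 0.497–0.502 |
| 0.6 | 0.544 | 0.577 | 0.501 |

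At SD 0.6 the differences are 0.544 − 0.501 = 0.043 and 0.577 − 0.501 = 0.076. The same random-fold scores evaluated within each clinic gave AUCs of 0.469 to 0.486 in all settings, slightly under chance. The apparent gain is therefore entirely between clinics.

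**3. Precision of the added analysis**

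Hanley–McNeil standard error at AUC 0.61 with 130 patients, 46 of them remitted (35% assumed): Q₁ = 0.61/1.39 = 0.439 and Q₂ = 2 × 0.61²/1.61 = 0.462.

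Variance = [0.61 × 0.39 + 45 × (0.439 − 0.372) + 83 × (0.462 − 0.372)] / (46 × 84) ≈ 0.00278, so SE ≈ 0.053 and the 95% half-width is about 0.10 for one clinic. For 73 patients (26 remitted) the half-width is about 0.14. Averaged over six clinics of 130 it is roughly 1.96 × 0.053/√6 = 0.04. Loss to follow-up is ignored and would widen all of these.

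**The case against.** The strongest reply has four parts.

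- **Random folds are not biased for new patients of these clinics.** This stands. The gap between pooled and within-clinic AUC reflects a different estimand. A reader might infer that random folds are a form of data leakage and that the article's statement about leakage is false. The documents do not support that: the statement concerns separating tuning from testing, which nested folds do.
- **The large figures need extreme inputs.** This largely stands. No listed baseline predictor names the clinic. Change of residence and income appear only as follow-up registry data, so they cannot be counted as predictors. Clinic remission rates from 18% to 57% within one region would be surprising. Background calls the package nationally uniform, and central assessment removes scanner and tester differences.
- **The article defers detail.** It promises more specific analysis plans, and nothing shown excludes a clinic-wise check. However, it does not leave the splitting rule open: it names random folds.
- **A held-out clinic from the same region is not a different cohort.** True, and leave-one-clinic-out does not replace external validation. It is the closest test these data allow, and it is closer to the article's own standard than random folds.

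Two further inferences are tempting. First, that therapy differs by clinic: the text says "clinics also offer alternatives to CBT, e.g., psychodynamic and schema therapy", but speaks of the clinics in general and does not say that the offer varies between them. Second, that therapy groups of eight should be kept whole within folds. Starts are about 1,100 × 0.88 = 968 a year, or 3,872 to 4,840 over four to five years (assumed). Then 800 participants are 17–21% of starts, or about 1.3 to 1.7 per group of eight on average, so keeping groups whole would change little.

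**Conclusion.** The point holds as a cheap and worthwhile improvement. Six treating clinics with different catchments, combined with random folds as the only stated validation, leave two questions unanswered: how much of the performance is patient-level, and whether the model transports to another clinic.

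The size cannot be derived from the article and is probably small. Under the assumed inputs the AUC excess is about zero when clinics differ little (SD of log-odds 0.2 or less), up to about 0.01 when features encode clinic weakly, and about 0.065 when features identify the clinic and clinics differ strongly. The corresponding extreme without any patient-level signal is 0.076. These figures rest on 35% remission in Set-up B and the implied clinic rates, near-equal clinics in Set-up B, and a ridge logistic model. Another learner could give other values.

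A reader might conclude that calling the cohort single-site is an error. It is defensible for baseline assessment and does not describe recruitment or treatment, so it needs clarification only.

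**What to change.** 1. Keep the randomized nested k-fold result as the estimate for future patients of these six clinics.
2. Beside it, for hypotheses 1.1, 1.2 and 2.2, report leave-one-clinic-out performance: AUC and calibration in each held-out clinic and averaged, with all tuning done inside the training clinics. For 2.2, report the incremental gain in the same way.
3. Base any claim of generalizable prediction on the leave-one-clinic-out result, and state that it is still internal to one region.
4. Describe the cohort as having one assessment site and six recruiting and treating clinics.

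This takes six more outer model fits per classifier, on data already collected, and changes no study procedure. It can go into the analysis plans the article promises before detailed analyses begin. The costs are wide intervals for single clinics (about ±0.10 AUC with 130 patients, wider in subcohort I) and possibly a less favourable figure. A difference of 0.01 between the two validations would not be resolvable and should not be over-read; one of 0.05 or more would be worth explaining.

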#### Hypothesis-driven analyses

To answer the hypothesis-driven research questions, i.e., hypotheses 3.1 – 3.4, we will use appropriate parametric models, including multiple linear regression or linear latent variable models to investigate group differences in [^11^C]-UCB-J binding between patients and HCs and multiple linear regression to determine associations between cognitive scores and [^11^C]-UCB-J binding in patients. We will adjust for age and sex, as our current data on HCs with [^11^C]-UCB-J are of equal sex distribution with a mean age of approximately 30 years old, which is not expected for the patient sample expecting to be predominately women and below 25 years old (Supplementary Fig. 1). Furthermore, dependent on additional funding, we will include more HCs and attempt to match their age distribution with the patients better.

We will also use statistical models such as logistic regression to investigate associations between individual measures and dichotomous clinical outcomes (e.g., the association between early childhood trauma and treatment response) when testing secondary hypotheses. Lastly, we will assess the associations between baseline patient characteristics, treatment events, and clinical outcomes using path analysis, enabling us to estimate the effect of treatments over time on the clinical outcome.

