**Methods:**

All patients are examined before receiving a standardised treatment package for adults aged 18–65 with first-episode depression in six public outpatient clinics in the Capital Region of Denmark. From this population, we will recruit a cohort of 800 patients for whom we will acquire clinical, cognitive, psychometric, and biological data. A subgroup (subcohort I, *n* = 600) will additionally provide neuroimaging data, i.e., Magnetic Resonance Imaging, and Electroencephalogram, and a subgroup of patients from subcohort I unmedicated at inclusion (subcohort II, *n* = 60) will also undergo a brain Positron Emission Tomography with the [^11^C]-UCB-J tracer binding to the presynaptic glycoprotein-SV2A. Subcohort allocation is based on eligibility and willingness to participate. The treatment package typically lasts six months.

Depression severity is assessed with the Quick Inventory of Depressive Symptomatology (QIDS) at baseline, and 6, 12 and 18 months after treatment initiation.

The primary outcome is remission (QIDS ≤ 5) and clinical improvement (≥ 50% reduction in QIDS) after 6 months. Secondary endpoints include remission at 12 and 18 months and %-change in QIDS, 10-item Symptom Checklist, 5-item WHO Well-Being Index, and modified Disability Scale from baseline through follow-up. We also assess psychotherapy and medication side-effects.

We will use machine learning to determine a combination of characteristics that best predict treatment outcomes and statistical models to investigate the association between individual measures and clinical outcomes.

We will assess associations between patient characteristics, treatment choices, and clinical outcomes using path analysis, enabling us to estimate the effect of treatment choices and timing on the clinical outcome.

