### Hypotheses

#### The entire cohort

Primary hypotheses:1.1 Clinical, cognitive, psychometric, genetic, and blood biomarker measures at inclusion can predict clinical remission (defined as QIDS ≤ 5) at the first follow-up.1.2 Clinical, cognitive, psychometric, genetic, and blood biomarker measures at inclusion can predict clinical improvement (a ≥ 50% reduction in QIDS from pretreatment) at the first follow-up.

Secondary hypotheses:1.3 Composite scores across a range of clinical, cognitive, psychometric, genetic, and blood biomarker measures at inclusion can cluster patients into MDD subgroups associated with treatment trajectories and outcomes.1.4 Clinical, cognitive, psychometric, genetic, and blood biomarker measures at inclusion are associated with clinical outcome defined as a change in QIDS.1.5 Path analysis of baseline patient characteristics and treatment tracks can uncover causal paths for clinical improvements, i.e., estimate the effect of treatment on clinical outcomes.

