### Data collection

The patients will undergo a multi-modal investigative program at inclusion and will be followed up after treatment and 12 and 18 months after treatment initiation with questionnaires assessing clinical status (Figs. 1 and 2). Apart from follow-up measures and information extracted from patient files and Danish health and social registries, all data collection will occur before the patient starts treatment.

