#### Follow-up

Patient-reported outcome measures assessing depression symptom severity and clinical status are sent via the national secure mail platform at three time points: 6, 12 and 18 months after treatment start (Table 4). Complete registry follow-up is done at 18 months as well.

**Table 4 Tab4:** Follow-up Measurements ^a^Omitted if the patient did not receive antidepressant medication

Measures	6 months	12 months	18 months
Quick Inventory of Depressive Symptomatology (QIDS-SR)	X	X	X
BSI-18, SCL-10, WHO-5 and mSDS	X	X	X
Patient-Reported Inventory of Side-Effects (PRISE)[51]^a^	X	X	X
Negative Effects Questionnaire (NEQ)	X		

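### Path analysis is said to yield causal effects of treatment choice and timing, but no severity measure is scheduled between baseline and 6 months, so effects of treatment changes in that window are expected to be confounded by indication

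*Protocol article*

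**What the plan says.** **The claim.** Hypothesis 1.5 (Hypotheses, The entire cohort) states: "Path analysis of baseline patient characteristics and treatment tracks can uncover causal paths for clinical improvements". The abstract's Methods paragraph describes the analysis as "enabling us to estimate the effect of treatment choices and timing on the clinical outcome". Statistical analyses, Hypothesis-driven analyses, lists the inputs as baseline characteristics, treatment events and clinical outcomes. It opens by calling the analysis one of associations and ends by "enabling us to estimate the effect of treatments over time on the clinical outcome". The Discussion again says the project will uncover causal paths for treatment response.

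**The measurement schedule.** The abstract says: "Depression severity is assessed with the Quick Inventory of Depressive Symptomatology (QIDS) at baseline, and 6, 12 and 18 months after treatment initiation". The Follow-up section sends the outcome questionnaires "at three time points: 6, 12 and 18 months after treatment start". Under Data collection, apart from follow-up measures, patient files and registers, "all data collection will occur before the patient starts treatment".

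**The treatment schedule.** The package typically lasts six months. Under Study population, "Medication is available as needed". In 2019-2020, 37% of patients were on an antidepressant at package start and 54% at its end. The Background says that guidelines make severity the main or only basis for choosing treatment.

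**The concern.** Within the package, exposure is to be dated finely from records and registers: sessions, drug, dose, switches. The likely main driver of exposure changes, how depressed the patient is at that moment, has no scheduled measurement. A model with baseline characteristics, treatment events and the 6-month outcome then mixes the effect of a change with the reason for it. If worsening patients are the ones started or switched, the estimate is pushed against the treatment.

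At stake is what the study may conclude about treatment choice and timing in the months when most package treatment is delivered. The article hopes to suggest treatment response algorithms that aid treatment choices, so a confounded coefficient reported as an effect could be carried forward.

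**Working it through.** The article gives no power or effect size for the path analysis, so there is no stated figure to reproduce. The check sets the two schedules side by side and then illustrates the possible size of the bias.

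**1. Schedules**

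| Months | Treatment | Scheduled severity |
|---|---|---|
| 0 | package starts; 37% already medicated | QIDS |
| 0-6 | therapy; drugs started or changed as needed | none |
| 6 | package typically ends; 54% medicated | QIDS |
| 12, 18 | later care | QIDS |

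**2. How many patients are involved**
- Net rise in antidepressant use: 54% − 37% = 17 points; 0.17 × 800 = 136 patients.
- Unmedicated at start: 0.63 × 800 = 504.
- Share of these who start: 17/63 = 27%.

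This applies the 2019-2020 rates to the planned cohort and assumes that nobody stops. Switches and dose changes are extra.

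**3. Size of the bias if the true effect is zero**

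When interim severity is left out of a linear model that adjusts for baseline severity:

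bias = k × g

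- k is the coefficient of interim severity on 6-month severity.
- g is the gap in interim severity between starters and non-starters, after adjusting for baseline.

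Assumptions, none of them from the documents: baseline-interim correlation 0.5; k = 0.5 to 0.7; a direct baseline coefficient of 0.1; QIDS SD of 5; log-odds of starting rising by 0 to 1.0 per SD of interim severity. The share starting is 27%. The gap g was obtained by simulating 1,000,000 patients.

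| Log-odds per SD | g (SD) | Bias = k × g (SD) | QIDS points (× 5) | z with 400 patients |
|---|---|---|---|---|
| 0 | 0 | 0 | 0 | 0 |
| 0.25 | 0.185 | 0.09-0.13 | 0.5-0.65 | 0.9-1.3 |
| 0.5 | 0.36 | 0.18-0.25 | 0.9-1.3 | 1.7-2.5 |
| 1.0 | 0.66 | 0.33-0.46 | 1.65-2.3 | 3.1-4.6 |

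Positive bias means that starters look worse. The 400 is also assumed: 504 unmedicated patients less one fifth without a 6-month score is 504 × 0.8 = 403. Adding interim severity to the model returns the estimate to zero in every row.

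**4. Size of the bias if the treatment truly helps**

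With a true effect of −1.5 QIDS points, k = 0.6 and baseline-interim correlation 0.4 to 0.6, adjustment for baseline alone gives:
- log-odds 0.25: −0.87 to −1.03
- log-odds 0.5: −0.28 to −0.57
- log-odds 1.0: +0.68 to +0.23

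Adding interim severity restores about −1.5 each time.

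**The case against.** **Interim severity may exist in the records.** Patient files and registers are exempt from the baseline-only rule, and records are extracted during treatment. The list of record items need not be complete. The article calls SCL-10, WHO-5 and mSDS the service's established effect parameters. It does not say whether clinics score them during the package. This stands: what can be said is that no interim measure is scheduled or listed for this use, not that none exists. The fix allows for it.

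**The size is assumed.** This also stands. Some starts may follow the initial workup and hence measured baseline severity. If half did, the bias over log-odds 0.5 to 1.0 would roughly halve, to 0.09-0.24 SD.

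**Details belong in a later plan.** The article promises specific analysis plans, and the choice between weighting, the g-formula and similar methods can wait for them. But no later model can restore a confounder that was never recorded, and the causal claim is already in print.

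**It is one secondary hypothesis.** True. The prediction hypotheses and the PET comparison do not rest on it. The claim nevertheless stands in the abstract, and the only bias handling the article names concerns selective participation and attrition.

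**Stronger readings.** A reader might infer that effective treatment will look harmful. In the working the sign reverses only at log-odds 1.0; at 0.25 and 0.5 the benefit is attenuated but still visible. A reader might also infer that staying in therapy will look beneficial. The documents do not support a direction: QIDS is sent at fixed times whether or not the patient remains in therapy, and patients may leave because they are better or because they are worse.

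**Conclusion.** The concern holds for treatment changes between baseline and 6 months. From the inputs the article lists, their causal effect is not identified, and confounding by indication is expected. It is not certain: the bias vanishes if changes do not depend on interim severity given baseline. The article's own account of severity-based choice and as-needed medication makes that unlikely. Under the assumed inputs and a true null, the bias is about 0.1 to 0.5 SD, or roughly 0.5 to 2.3 QIDS points at an SD of 5. The documents fix neither end of that range.

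The problem is smaller, but not absent, elsewhere. Choices at package start can be adjusted for baseline QIDS in patients unmedicated at that point. For the 37% already on an antidepressant, baseline QIDS is itself measured after treatment began. Changes soon after the 6- and 12-month assessments have a recent score; changes late in those intervals again do not.

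**What to change.** 1. In the abstract, hypothesis 1.5, Hypothesis-driven analyses and the Discussion, describe path coefficients for treatment events in months 0-6 as associations. The exception is if dated in-treatment severity scores can be extracted from the medical records and used as time-varying confounders. Establish whether such scores exist before the analysis plan is fixed.
2. Add a sensitivity analysis for unmeasured confounding of these coefficients.
3. Limit effect language to decisions close to a QIDS assessment:
   - treatment started at package start in patients unmedicated at baseline, adjusted for baseline QIDS and other baseline confounders;
   - changes made soon after the 6- and 12-month assessments, adjusted for QIDS at that visit.
4. State that patients already medicated at package start (37% in 2019-2020) have a post-treatment baseline QIDS.

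The cost is a narrower causal claim, some rewording and one sensitivity analysis. No new visits are needed, and the primary prediction hypotheses are untouched.
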